## Abstract

**Background:**

There is a lack of evidence on the effectiveness of livelihood interventions amongst people with disabilities. In many countries, self-employment or microentrepreneurship is a dominant source of livelihoods for people with disabilities and their caregivers. However, this group may face heightened barriers to successful microentrepreneurship, including discrimination, exclusion from training or inaccessible transport, infrastructure and communication systems. The InBusiness programme is a livelihoods programme targeted to microentrepeneurs with disabilities or their caregivers delivered by a consortium of non-governmental organisations. The programme focuses on improving the skills, practices and opportunities of microentrepreneurs while linking them with procurement opportunities with private and public institutions. This protocol describes a randomised controlled trial of the InBusiness programme in eight counties of Kenya.

**Methods:**

The randomised controlled trial will involve 495 microentrepreneurs who have been verified as eligible for InBusiness by programme implementers. Individuals will be randomised within counties, either being invited to enrol in InBusiness in March 2023 or allocated to a control group. Participants in the control arm will receive information about compliance with business-related laws and available social protection programmes. The trial will assess the impact of InBusiness on household consumption and individual economic empowerment (primary outcomes) as well as food security, well-being, social attitudes, unmet need for disability-related services and microenterprise profits (secondary outcomes). Baseline was conducted in March 2023, and follow-up will be 24 months from baseline (12 months from completion of the programme). Analysis will be through intention to treat. A process evaluation will explore fidelity, mechanisms of impact and the role of context, and complementary qualitative research with participants will be used to triangulate findings across the trial.

**Discussion:**

This study will provide evidence on the impact of a large-scale disability-targeted livelihood programme on household and individual financial security and well-being. Currently, there is a lack of evidence on the effectiveness of livelihood programmes amongst people with disabilities, and so this trial can help inform the design and delivery of InBusiness as well as other livelihood programmes targeted to people with disabilities.

**Trial registration:**

ClinicalTrials.gov ISRCTN13693137. Registered on April 24, 2023.

**Supplementary Information:**

The online version contains supplementary material available at 10.1186/s13063-023-07848-2.

## Introduction

### Background and rationale

The 2022 Kenya Demographic and Health Survey estimates that almost 6% of the population of Kenya has a disability [1]. The Kenya Persons with Disabilities Act of 2003 and its 2012 revision defines disability as a “physical, sensory, mental or other impairment, including any visual, hearing, learning or physical incapability, which impacts adversely on social, economic or environmental participation” [2]. The true prevalence of disability is likely to be higher, as recent WHO estimates suggest that 16% of the world’s population are people with disabilities [3]. Both globally and in Kenya, people with disabilities are more likely to be living in poverty and excluded from livelihood opportunities compared to people without disabilities [1, 4, 5]. Improving access to decent work and alleviating poverty “for all” are key aims of the Sustainable Development Goals [6] and are in line with national policies in Kenya [2].

Self-employment, or microentrepreneurship, is a major source of livelihoods in low- and middle-income countries. In Kenya, there were approximately 7.41 million microenterprises in 2016, accounting for 34% of Kenya’s GDP and employing over 14.9 million people [7]. The participation of people with disabilities in Kenya in this sector is unclear, but if following international trends, it is likely to represent a significant livelihood source for people with disabilities due to widespread exclusion from waged employment [8, 9]. There are some social protection measures in Kenya to improve opportunities for microentrepreneurs with disabilities, such as the access to public procurement opportunities programme. This programme sets aside 30% of annual government procurement budget for businesses run by people with disabilities, youth and women, of which at least 2% is reserved for people with disabilities. However, this quota is often underfilled, with only 1.3% of the budget was awarded to firms owned by people with disabilities in 2018 [10].

People with disabilities and their caregivers may face additional barriers to successful microentrepreneurship, leading to job insecurity and low and unstable earnings [11]. For example, people with disabilities may lack skills and training from earlier exclusion from education [9]. Further, discrimination and poor informational, communication and infrastructure accessibility of linked systems (e.g. transport, places to buy inputs/sell outputs) can limit opportunities for growth. Meanwhile, caregivers of people with disabilities can face both opportunity and direct costs associated with caregiving, reducing time and resources available to invest in their microenterprises. Improving the management and profitability of microenterprises run by people with disabilities and caregivers of people with disabilities may help to increase their livelihoods and financial security. However, a recent systematic review found a lack of evidence on the impact of interventions designed to improve livelihoods for people with disabilities and their households, and available evidence was often of poor quality [12].

Consequently, this study will conduct a randomised controlled trial (RCT) of the InBusiness programme in Kenya. InBusiness is run by a consortium of non-governmental organisations (NGOs) — Light for the World (LftW), Humanity & Inclusion (HI) and Sense International (SI). The programme aims to improve the skills of microentrepreneurs with disabilities and microentrepreneurs who are caregivers of people with disabilities, through mentorship and classroom trainings. It also facilitates pathways for expanding their microenterprises, such as through increased procurement opportunities with public and private institutions (PPIs) and transfers of business-related assets. The programme is being implemented in eight counties in Kenya and has potential for wider scale-up in Kenya and other settings.

### Aims and objectives

The overall aim of the research is to assess the impact of InBusiness on improving social and economic wellbeing of people with disabilities and their households. Specific objectives include the following:To assess the impact of InBusiness on household per capita expenditures and economic empowermentTo evaluate the impact of InBusiness on quality of life and access to key disability-related goods and servicesTo explore the aspects of InBusiness that were perceived to be most important for achieving impacts amongst participantsTo examine barriers and enablers to the implementation and delivery of InBusiness from the perspective of participants and implementers.

## Methods and analysis

### Design

The study’s main design is an individual, superiority RCT of the LftW-led component of the InBusiness programme.^1^ It follows the SPIRIT guidelines for RCTs (Supplemental file 1). The LftW InBusiness programme is being implemented in 8 of 47 counties in Kenya. Individuals applying to InBusiness will be randomised to either the intervention or control group. The intervention group will be offered a place on the InBusiness programme for enrolment in March 2023. The control group will not be offered a place on the InBusiness programme but will receive information about compliance with business laws and on available social protection programmes. Baseline data collection will be conducted before randomisation and before participants are invited to enrol in InBusiness to minimise anticipatory behaviour. Follow-up will be conducted 24 months after baseline (12 months after the completion of the delivery of InBusiness).

The RCT will be complemented with a process evaluation and qualitative research. In-depth interviews will be conducted with participants in both study arms after the delivery of InBusiness is completed to explore their experiences of running a microenterprise, and for the intervention arm, and of participating in the InBusiness programme. In-depth interviews with programme implementers will also be conducted, and monitoring data from InBusiness and the endline of the RCT will be reviewed to explore the implementation fidelity, mechanisms of impact and contextual factors that can affect variations in outcomes. The process evaluation will use the Medical Research Council guidance for process evaluations of complex interventions as a framework [13].

### Eligibility criteria

Participants in both the control and intervention arms must meet InBusiness’ eligibility criteria. Eligibility for the InBusiness programme is based on the following: (1) Has a disability or is the caregiver of a person with a disability. Disability is defined as having a disability identification card issued by the national government (i.e. registered with the National Council for Persons with Disabilities), (2) lives and operates a microenterprise in one of the eight counties covered by the InBusiness programme, (3) has a business licence/permit or is in the process of applying for a permit, (4) has a microenterprise that has been in existence for at least 6 months, and (5) microenterprise has a monthly income of at least KES 10,000 (US $75). For past recruitments, these criteria have sometimes been relaxed slightly to obtain sufficient numbers of participants.

The identification process was conducted through a call for applications led by LftW, HI and SI. Calls for applications were distributed through Organisations of Persons with Disabilities (OPDs) through the umbrella OPD United Disabled Persons Kenya. Overall, 776 met programme eligibility.

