### Recruitment and randomisation

Recruitment is through self-selection with LftW verification. LftW circulated calls to apply for the InBusiness programme in the eight counties where it will be operating in. Individuals submitted an application, and LftW verified if they meet eligibility criteria.

LftW has funding to provide the programme to approximately 480 people across two cohorts (cohort 1: enrolment in March 2023 and cohort 2: enrolment in March 2024). LftW verified 776 eligible people between December 2022-February 2023. Within this group, individuals will be randomised to either cohort 1, cohort 2 or the control group (Fig. 1). The RCT will focus on cohort 1 (intervention group) and the control group. Cohort 2 will not be part of the RCT as they will not have been involved in the project for sufficient time at follow-up.

Randomisation will take place in two phases. Individuals will first be randomised to either cohort 2 or the group taking part in the RCT. Baseline data will then be collected from the RCT group, after which individuals will be randomised to cohort 1 or the control group. Randomisation will be within counties based on quotas from LftW on the number of placements available for cohorts 1 and 2, and each group will be roughly balanced by gender. Randomisation will be done through R by staff at the London School of Hygiene & Tropical Medicine (LSHTM).

If there are a small number of dropouts in people randomised to cohort 2 (< 20 individuals), LftW can recruit from the control group to avoid needing to re-advertising and re-verifying applicants. In this instance, individuals moving from control to cohort 2 will be selected randomly and will be excluded from the analysis.

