### Intervention

The InBusiness programme seeks to improve the social and economic wellbeing of MEs with disabilities and their households. The programme primarily targets people with disabilities who are the primary owner of a microenterprise but in a minority of cases will offer the programme to businesses run jointly by a people with disabilities and a caregiver or businesses run only by a caregiver of an adult/child with a disability. The programme provides business, technical, self-advocacy and compliance skills training and in-kind transfers of assets required to expand the business named “business growth kits” and facilitates procurement opportunities with PPIs.

The InBusiness programme will be delivered over 10 months. The core components include the following:Classroom-based trainings: Microentrepreneurs will receive classroom training on skills to improve their business practices. Content covered in trainings includes record keeping, compliance with national and local regulations and self-advocacy.Capacity building: One-to-one follow-up with microentrepreneurs to monitor their progress and implementation of trainings and to offer tailored advice to support their businesses.Business growth kits: Microentrepreneurs will be provided with an in-kind asset to grow or improve the profitability of their business and/or support their participation in the business (e.g. assistive products). The asset will be tailored based on the needs of each microentrepreneur’s business and/or accessibility needs.PPI disability inclusion training: PPIs will be trained on disability inclusion and encouraged to offer procurement opportunities to people with disabilities (e.g. through the access to public procurement opportunities programme).Linking to procurement opportunities: Microentrepreneurs will be made aware of and supported to apply for procurement opportunities with local PPIs.

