### Data collection

Data for the RCT will be collected using questionnaires completed by participants in the intervention and control arms at baseline and endline. Data collection will be conducted in a place of the participants’ choosing (e.g. home, business). The questionnaire is based upon standard modules and from modules used in other studies (Table 1). It includes sections on the following: household composition, housing conditions, food security, savings and expenditures; individual economic empowerment, well-being and access to services; and microenterprise revenues, costs and practices. It was reviewed by programme implementers and piloted with individuals who had previously participated in the InBusiness programme to check for acceptability and understanding before full-scale data collection. The survey will take approximately 1 h to complete and will be delivered by trained enumerators using Open Data Kit (ODK).

**Table 1 Tab1:** Outcome indicators for the RCT of the InBusiness programme

Outcome indicator	Description	Source
*Primary outcomes*		
Household consumption	Overall per capita household consumption and domains of expenditures (food, health) adjusted for inflation	Adapted version of [14]
Economic empowerment	Score on a 14-item financial self-efficacy tool	Adapted version of [15]
*Secondary outcomes*		
Subjective wellbeing	Total score on a 7-item tool on self-reported well-being	Adapted version of [16]
Food security	Proportion classified as facing moderate or severe food insecurity	Food Insecurity Experience Scale [17]
Social attitudes	Total score on 9-item tool on social attitudes	World Health Model Disability Survey [18]
Unmet need for disability-related goods and services	Self-reported unmet need for disability-related healthcare, assistive devices or assistance	Tool developed for study
Microenterprise profits	Net of revenues minus costs, adjusted for inflation	Tool developed for study

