### Sample size

One of primary outcome measures is household expenditure per capita. Using data from the Kenya Integrated Household Budget Survey (KIHBS) 2015/2016 [19], we assume an average household per capita expenditures of 7811 KSH. Standard deviation was not presented in the report, but we assume standard deviation of 40% of the mean (3124 KSH). With power of 80% and type 1 error of 5%, we would need a total sample size of 398 (199 per arm) to detect an effect change of 10% of household expenditure per capita. Assuming a loss to follow-up of 20% and a potential switch of 20 individuals from control group to cohort 2 (excluded from RCT analysis), we will need to recruit at least 497 individuals.

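### Co-resident applicants can be randomised to opposite arms although the sized primary outcome is a household measure; any such split dilutes the consumption effect, probably modestly

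*Protocol article*

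**What the plan says.** The Design section sets the unit: "The study’s main design is an individual, superiority RCT of the LftW-led component of the InBusiness programme". Under Eligibility criteria, the first criterion admits a person who "Has a disability or is the caregiver of a person with a disability". The other four concern county, permit, age of the business and monthly income. None limits entry to one applicant per household.

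Under Recruitment and randomisation, people apply as individuals and are allocated in two phases: cohort 2 versus the trial group, then cohort 1 versus control. The stated constraints are county and gender: "Randomisation will be within counties based on quotas from LftW on the number of placements available for cohorts 1 and 2", with groups roughly balanced by gender. Household is not mentioned.

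Table 1 (Data collection) defines the first primary outcome as "Overall per capita household consumption and domains of expenditures (food, health) adjusted for inflation" and the second as "Score on a 14-item financial self-efficacy tool". The Sample size section uses only the first: "we assume an average household per capita expenditures of 7811 KSH". Food security is listed among the household parts of the questionnaire, so it may be a household measure too, although Table 1 does not say so. The Data analysis section adjusts for the baseline outcome, stratification variables and imbalanced variables, and does not mention households.

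**The concern.** The unit randomised is the person, while the unit measured for the sized outcome is the household. This does no harm when each household supplies one participant. It matters when two co-resident people, for example a person with a disability and a caregiver who each run a qualifying microenterprise, are both verified. Randomised independently, one can enter cohort 1 and the other the control group. Both then report the same household's consumption, once as treated and once as untreated. The household is not an untreated comparator, and it contributes nothing to the difference between arms.

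The resulting error has a direction. It shrinks the consumption effect, and any food security effect measured at household level. Neither longer follow-up nor better retention removes it. An analysis can identify the affected households, but it cannot undo a split allocation.

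**Working it through.** **Inputs from the Sample size section.** Mean 7811 KSH; SD 3124 KSH; effect 10%, so δ = 781.1 KSH; power 80%; type 1 error 5%, sidedness not stated; 199 per arm, 398 in total.

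**Input not in the document.** f, the share of trial participants with a household member who is also in the trial. I assume a range of 1% to 20%.

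**Step 1: reproduce the planned size.** n per arm = 2 × (SD/δ)² × (z_α + z_β)², with 2 × (3124/781.1)² = 31.99.

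- One-sided 5%: 31.99 × (1.645 + 0.842)² gives 198 per arm; the t-based figure is 199, as stated.
- Two-sided 5%: 31.99 × (1.960 + 0.842)² gives 252 per arm; the t-based figure is 253.

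The stated 199 therefore fits a one-sided test only. That is a separate matter, but it is why both power columns appear below.

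**Step 2: dilution.** With about 1:1 allocation and independent draws, about half of co-resident pairs are split, so a share f/2 of each arm belongs to split households. Write h for the mean consumption of those households, which is the same in both arms, and μ for the untreated mean.

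- Treated mean = (1 − f/2)(μ + δ) + (f/2)h
- Control mean = (1 − f/2)μ + (f/2)h
- Difference = δ(1 − f/2)

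At f = 5% this is 781.1 × 0.975 = 762 KSH. At f = 10% it is 781.1 × 0.95 = 742 KSH.

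**Step 3: power at 199 per arm.** Same-arm pairs raise the variance of the difference and split pairs lower it. With half of each and identical consumption within a household, the two cancel. The standard error stays at 3124 × √(2/199) = 313 KSH, and only the effect changes.

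| f (assumed) | Expected effect | Power, one-sided 5% | Power, two-sided 5% |
|---|---|---|---|
| 0 | 10% | 80.2% | 70.3% |
| 1% | 9.95% | 79.9% | 69.9% |
| 2% | 9.90% | 79.5% | 69.5% |
| 5% | 9.75% | 78.4% | 68.1% |
| 10% | 9.5% | 76.6% | 65.9% |
| 20% | 9.0% | 72.6% | 61.2% |

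**Step 4: what f means in people.** Of 398 analysed participants, f = 5% is about 20 people, or 10 pairs, of which about 5 are split. f = 10% is about 40 people, 20 pairs, and about 10 split.

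**The case against.** The strongest reply is that this point rests on silence. The article is condensed, and a one-per-household check could sit in the full protocol or in the implementer's verification procedure. Clustered errors and sensitivity analyses belong in the analysis plan, which is promised before endline. No co-enrolled household is reported, and nothing says that caregivers and the people they care for usually live together or both apply. Caregivers of children cannot form a pair with the child, because all participants are over 18. A pair also needs two applicants who each meet the business criteria.

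Much of this stands. It makes the size unknown and probably small. It does not remove the point: the article sets out all five criteria, both phases, the quotas, the gender balance and even the rule for a few controls moving to cohort 2, and under those rules co-resident applicants can be split.

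A reader might go further in three ways that the document does not support.

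- **Same business in both arms, so profits are counted twice.** The Intervention section says the programme "in a minority of cases will offer the programme to businesses run jointly by a people with disabilities and a caregiver". That reads as one offer per jointly run business, so two places for one enterprise are not what it describes.
- **The primary effect as a whole is biased.** Economic empowerment is an individual score, so double counting of a household does not reach it.
- **A dilution of 0.62f.** This takes 480/776 = 62% as the chance that a control's partner gets a place in either cohort, giving about 9.7% and 9.4% at 5% and 10%. It credits cohort 2 with the full benefit, whereas the Recruitment section leaves cohort 2 out of the trial because its exposure by follow-up will be too short.

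**Conclusion.** The point holds in conditional form. As the article stands, co-resident applicants can be allocated to opposite arms, and nothing stated prevents or handles this. If it happens, the effect on household consumption, and on food security if measured per household, is pulled toward zero. It cannot be said that the effect is in fact biased, because the number of shared households is not given.

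The likely loss is modest: a 10% effect becomes 9.75% at f = 5% and 9.5% at f = 10%. Power falls by about 1.8 and 3.6 points one-sided (80.2% to 78.4% and 76.6%), or 2.2 and 4.4 points two-sided. These figures assume 1:1 allocation, half of pairs split, identical consumption within a household, and the same household benefit whether one or two members are enrolled. The values of f are assumptions. This is a worthwhile, inexpensive improvement rather than a flaw that threatens the trial.

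**What to change.** In the design, randomise verified applicants from the same household as one unit in both phases, or admit one applicant per household, and say so. If the full protocol already has such a rule, one sentence in the article closes the matter.

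Recruitment ended in March 2023, so where allocation is already done:

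1. Identify shared households within the trial from application data and the baseline household-composition module, and report how many there are and how many are split between arms.
2. Use household-clustered standard errors.
3. For household outcomes, add a sensitivity analysis that excludes households with more than one trial participant, as known before the cohort 1/control randomisation. Baseline is collected before that step, so the restricted comparison remains randomised.

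Partners in cohort 2 have no trial baseline survey and can be checked only as far as the application data allow.

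The cost is a record match, a short addition to the analysis plan and slightly fewer records in the restricted analysis.
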